
## Methods

### Study aims

The first primary aim of this study was to create preliminary German versions of the CCAS Scale. The second primary aim will be their validation in a large cohort of patients with various cerebellar disorders and healthy age-, sex-, and education-matched controls. Secondary aims will be to examine possible relationships between clinical features such as disease duration or severity of cerebellar motor symptoms, and the CCAS score.

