**Degenerative Cerebellar Disorders**		
**Cer-pure** Disorders primarily affecting the cerebellum	- SAOA - EA1 and EA2 - SCA6 - SCA8 - SCA14 - ANO10 - Post-inflammatory cerebellar degeneration	
**Cer-plus** Disorders with relevant extracerebellar involvement	- MSA-C - all other hereditary ataxias including: SCA1, 2, 3, Friedreich’s ataxia, early onset cerebellar ataxias	

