**Focal Cerebellar Lesions**		
**Cer-pure/ cer-plus**	- Cerebellar stroke - Cerebellar hemorrhage - Cerebellar tumor - Cerebellar surgical lesion	
**Controls**	- General inclusion criteria	- General exclusion criteria - Neurological and psychiatric disorders
**Pretesting Subjects**	- General inclusion criteria	- General exclusion criteria - Neurologists and psychologists that were involved in the development of the German CCAS Scales

*Abbreviations*: *Cer-pure* Isolated Cerebellar Disease/ Lesion, *Cer-plus* Cerebellar Plus Disease/ Lesion, *SAOA* Sporadic Adult Onset Ataxia, *EA1* Episodic Ataxia Type 1, *EA2* Episodic Ataxia Type 2, *SCA1, 2, 3, 6, 8, 14* Spinocerebellar Ataxia Type 1, 2, 3, 6, 8, 14, *ANO10* Spinocerebellar Ataxia, Autosomal-Recessive Type 10, *MSA-C* Multisystem Atrophy Cerebellar Type, *CCAS* Cerebellar Cognitive Affective/ Schmahmann Syndrome

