##### Data analysis

Selectivity and sensitivity will be assessed using the same cut-off values for individual test items, and the same three pass/ fail criteria determined in the original study by Hoche et al. [10] (that is: possible CCAS = one test failed; probable CCAS = two tests failed; definite CCAS = three or more tests failed). To assess selectivity the percentage of true negatives will be calculated, that is the percentage of controls which have been correctly identified as controls [number of controls identified as controls/ true number of controls in the sample * 100]. To assess sensitivity the percentage of true positives will be calculated, that is the percentage of patients which have been correctly identified as patients [number of patients identified as patients/ true number of patients in the sample * 100]. In case selectivity and sensitivity falls below the values of the original CCAS Scale, selectivity and sensitivity of individual tests will be assessed. Cut-off values of single test items and/ or cut-offs defining (possible/ probable/ definite) CCAS will be adjusted to achieve high selectivity and reasonable sensitivity – comparable to the values of the original CCAS Scale.

Differences between patient groups (pure cerebellar disease vs. patients with additional extracerebellar involvement) will also be analyzed. We want to verify that difficulties in verbal registration and delayed verbal recall are indicative of extracerebellar involvement (“red flags”). In further accordance with Hoche et al. [10], Cronbach’s alpha will be used to assess the inter-relatedness of the individual test items, i.e. internal consistency.

To study construct validity of the CCAS Scale subtests of validated German versions of neuropsychological test batteries will be used as the external criterion. We will compare the percentage of patients diagnosed with CCAS based on a detailed neuropsychological test battery with the percentage of patients identified by the CCAS Scale.

Finally, correlations between age, disease duration, severity of cerebellar motor symptoms (measured by clinical ataxia scores), and total CCAS sum score will be calculated. All raw data (thus total number of failed tests respective total sum score and sub scores on single test items) will be tested for normal distribution using Kolmogorov-Smirnov tests. Parametric or non-parametric tests will be applied depending on distribution and final sample size.

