## Perspective

Clinical ataxia scales have been validated to rate the severity of motor symptoms in cerebellar disease [13–17], but so far there has not been a validated clinical scale to screen for the presence of the Cerebellar Cognitive Affective/ Schmahmann Syndrome (CCAS), and quantify CCAS severity. Only recently, Schmahmann and collaborators have developed and validated a promising screening tool for the CCAS – the CCAS Scale – for an American English-speaking population [10]. Till now, no validated German versions of the scale exist. German versions of the CCAS Scale are highly desirable to screen for the presence of CCAS in a clinical setting, but also for patient characterization and stratification in future therapeutical trials. The CCAS sum score may also serve as a therapeutic marker, but this would need future studies to show its sensitivity to change, and if this would be the case, its treatment responsiveness. In this multicenter study, four parallel versions (A-D) of the German CCAS Scale will be validated in a large cohort of German-speaking patients with cerebellar disorders. The parallel versions will allow multiple testing without practice effects.

The primary aim of our validation study is to show high selectivity, that is to show that the German versions of the scale are able to differentiate between patients and controls. We will test whether the pass/ fail criteria used to determine the presence of CCAS in the original scale also apply for the German scale. Cut-off values of individual test items and the pass/ fail criteria shown in Fig. 1 are taken from the US-American original and may change depending on findings in the German validation cohort. Furthermore, future studies are needed to test for possible age effects, and the need for age-dependent cut-off values and pass/ fail criteria. After full validation of the scale the implementation of a web-based training tool is planned.

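### Control matching does not balance cer-pure against cer-plus, so the red-flag comparison and the duration and severity correlations are open to confounding by age and education

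*Protocol article*

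**What the plan says.** Under Study aims, the protocol article plans validation against "healthy age-, sex-, and education-matched controls". Study sample makes the unit of matching explicit: one control per patient, of the same sex, within 5 years of age and in the same of five education bands. The same section asks for at least 25 cer-pure and at least 40 cer-plus patients. It assigns patients with degenerative disease by diagnosis, and sets no balance between the two patient groups.

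Table 1 places one category defined by adult onset in cer-pure ("Sporadic Adult Onset Ataxia") and one defined by early onset in cer-plus ("early onset cerebellar ataxias"). Both lists hold many other diseases, and focal lesions can fall in either group.

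Data analysis then states:
- "Differences between patient groups (pure cerebellar disease vs. patients with additional extracerebellar involvement) will also be analyzed".
- The purpose: "We want to verify that difficulties in verbal registration and delayed verbal recall are indicative of extracerebellar involvement".
- For the clinical features: "correlations between age, disease duration, severity of cerebellar motor symptoms (measured by clinical ataxia scores), and total CCAS sum score will be calculated".
- For the method: "Parametric or non-parametric tests will be applied depending on distribution and final sample size".

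No covariate, stratification or partial correlation is named. Years of education are recorded (Demographics and clinical assessment) but do not appear in the analysis.

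**The concern.** By matching on age, sex and education, the design itself treats them as relevant to the score. That protection covers the patient-control contrast. It does not carry over to comparisons made among patients, and the red-flag question and the clinical correlations are both of that kind.

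If cer-plus patients are younger than cer-pure patients and recall declines with age, a true red-flag effect can be hidden. If they are older, an age effect can pass for a red flag. Likewise, disease duration tends to be longer in older patients, so a correlation of duration with the sum score may partly or wholly reflect age. At stake are the interpretation of the two memory items as markers of extracerebellar involvement, and the study's stated secondary aim of relating clinical features to the CCAS score.

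**Working it through.** **Inputs from the protocol article.** Cer-pure n ≥ 25 and cer-plus n ≥ 40, and 25 + 40 = 65, which reproduces the stated minimum. No alpha, power, effect size or SD is given for these analyses, so there is no planned power figure to reproduce. The only age SD in a group that includes patients is 14.9 years, from the lay pre-test group. It is used here for illustration only.

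**Assumptions, not in the documents.** Two-sided 5% level, normal approximation, the age gap between cer-pure and cer-plus, and the strength of the age-score relation.

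**1. Precision of the red-flag comparison.** SE = sqrt(1/25 + 1/40) = sqrt(0.065) = 0.255 SD. The difference detectable with 80% power is (1.960 + 0.842) × 0.255 = 0.71 SD.

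**2. False red flag: no true difference, age acting alone.** Bias = |r(age, score)| × age gap / 14.9. Rejection rate = Φ(bias/0.255 − 1.96) + Φ(−bias/0.255 − 1.96).

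| Age gap | Bias, \|r\| 0.2 to 0.5 | Rejection rate |
|---|---|---|
| 0 years | 0 | 5% |
| 5 years | 0.07 to 0.17 SD | 6% to 10% |
| 10 years | 0.13 to 0.34 SD | 8% to 26% |
| 15 years | 0.20 to 0.50 SD | 12% to 51% |

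With r = 0 the rate stays at 5% whatever the gap.

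**3. Hidden red flag: a true difference of 0.7 SD, bias in the opposite direction.** Assume a decline of 0.015 to 0.03 SD per year and a gap of 10 to 20 years. The bias then runs from 10 × 0.015 = 0.15 SD to 20 × 0.03 = 0.6 SD. Power = Φ((0.7 − bias)/0.255 − 1.96).

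| Bias | Power |
|---|---|
| 0 | 78% |
| 0.15 SD | 58% |
| 0.3 SD | 35% |
| 0.6 SD | 6% |

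**4. Spurious correlation of duration with the sum score.** If age is the only link, spurious |r| = r(age, duration) × |r(age, score)|. With n = 65, the rejection rate is Φ(atanh(r) × sqrt(62) − 1.96) plus a negligible or small opposite tail.

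| r(age, duration) × \|r(age, score)\| | Spurious \|r\| | Rejection rate |
|---|---|---|
| 0.2 × 0.2 | 0.04 | 6% |
| 0.4 × 0.4 | 0.16 | 25% |
| 0.5 × 0.5 | 0.25 | 52% |

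**5. A tempting alternative remedy.** Analysing patient minus matched control removes the matched factors, but the variance becomes 2(1 − ρ) times that of a single score, where ρ is the within-pair correlation. Precision is lost unless ρ exceeds 0.5. For the same 0.7 SD:
- ρ = 0: SE = 0.255 × sqrt(2) = 0.361, power 49%.
- ρ = 0.2: SE = 0.255 × sqrt(1.6) = 0.322, power 58%.

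The second figure is no better than accepting a bias of 0.15 SD.

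**The case against.** The strongest reply is that the article is silent on covariates and does not actually prescribe an unadjusted analysis. A condensed article may leave the covariates of secondary analyses to a full protocol or SAP that is not shown. That is fair, and it keeps the point modest. But the section does name its methods, namely correlations and tests chosen by distribution and sample size. As written, these do not remove the confounding.

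Four stronger readings are tempting, and the documents do not support them.

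- *The secondary results are confounded.* No age or education imbalance between the groups is given, and no age-score relation. Only exposure to confounding is shown.
- *Cer-plus patients must be younger.* A reader might infer this from the adult-onset and early-onset entries in Table 1. Those are single entries in mixed lists: cer-plus also holds MSA-C and SCA1, 2 and 3, and cer-pure also holds the episodic ataxias. Age at onset is not age at testing, and all participants are adults. Neither size nor direction can be read off. For education there is no indication either way.
- *Age is ignored.* It is the first variable in the list of correlations. It is simply not used for adjustment.
- *Age adjustment is deliberately deferred.* The Perspective section says "future studies are needed to test for possible age effects", but it does so together with age-dependent cut-offs and pass/fail criteria. That concerns norming the scale. It is not a refusal to adjust the secondary analyses, and it does not show that the matched primary analysis is at fault.

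**Conclusion.** The point holds in a limited form. Patient-control matching does not balance cer-pure against cer-plus, and the analysis described does not adjust for age or education. The red-flag comparison and the duration and severity correlations are therefore open to confounding in either direction.

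The size cannot be determined from the documents. It is nil if the groups have similar ages or if age is unrelated to the scores. It reaches about 0.6 SD for the group comparison under a 20-year gap and a decline of 0.03 SD per year. The spurious correlation runs from 0.04 to 0.25 in absolute value when both component correlations lie between 0.2 and 0.5. All of these ranges rest on assumed values.

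The consequence is confined to secondary results. The primary analysis of selectivity and sensitivity uses matched controls and is not affected.

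**What to change.** In Data analysis, state that:

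- the cer-plus v cer-pure difference in verbal registration and in delayed verbal recall will be estimated by regression adjusted for age, years of education and sex;
- the associations of disease duration and ataxia severity with the sum score will be reported as partial (rank) correlations, or from regression, adjusted for the same three variables;
- unadjusted results will be shown alongside.

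Two additions are best kept out of the main analysis. The Inventory of Non-Ataxia Signs (INAS) closely tracks the extracerebellar involvement that defines cer-plus, so including it could adjust away the contrast under test. Use it at most in a separate sensitivity analysis. Patient-minus-control differences should not be the main analysis, because of the loss of precision shown above.

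Cost: a change of wording and no new data, since age and sex are needed for matching and education is recorded. The three covariates use three degrees of freedom. With 65 patients the residual degrees of freedom fall from 63 to 60 in the group comparison.

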## Background

Cerebellar disease results in well-known motor performance deficits, including ataxia of stance and gait, limb incoordination, dysarthria, and oculomotor abnormalities. During the last decades, there has been growing evidence that cerebellar disease is not only accompanied by motor disturbances but also by cognitive and affective symptoms (see [1–3] for reviews). As early as 1998, Schmahmann and Sherman introduced the *Cerebellar Cognitive Affective/ Schmahmann Syndrome (CCAS)* [4]*.* The core symptoms of CCAS are difficulties with executive, linguistic and visuospatial functions as well as problems with the regulation of emotion and affect. Since its original description, evidence for the presence of CCAS has been accumulating in pediatric and adult patients suffering from different cerebellar diseases including various hereditary ataxias, cerebellar tumors, and cerebellar stroke [1–3]. In recent years, advances in structural and functional brain imaging allowed for detailed mapping of cognitive functions in the posterolateral cerebellar hemisphere [5–9]. As yet, diagnosis of CCAS relies on non-standardized bedside cognitive examination and, if available, detailed neuropsychological test batteries. Until recently, there has not been a validated bedside test that was able to reliably screen for CCAS in cerebellar patients – unlike well-established bedside tests for dementias or mild cognitive impairment (MCI), i.e. Mini Mental State Examination (MMSE) or Montreal Cognitive Assessment (MoCA). However, MMSE and MoCA are of limited use to screen for CCAS because cerebellar patients frequently perform within the normal range [10]. Recently, Schmahmann and colleagues [10] have developed a bedside test designed to screen for CCAS in adults. In order to develop this CCAS Scale, they first applied a broad battery of 36 well-established neuropsychological tests in a large group of cerebellar patients primarily suffering from cerebellar degeneration. In the novel CCAS Scale, tests were implemented which captured the core cognitive domains of CCAS, distinguished best between cerebellar patients and controls, and at the same time were short and easy enough to be applied in a bedside setting. These include test items for semantic and phonemic fluency, category switching, verbal registration and delayed verbal recall, digit span forward and backward, cube draw and copy, similarities, go/ no-go, and affect. Single tests can either be passed reaching a specific cut-off score or failed. CCAS is considered possible if one test is failed, probable if two tests are failed, and definite if three or more tests are failed. Version A of the CCAS Scale has then been validated in another US-American cohort of 39 adult cerebellar patients, including patients with cerebellar degeneration and focal cerebellar lesions and 55 matched healthy controls. It exhibited high values for selectivity [that is the ability to distinguish between patients and controls, or in other words preventing controls from being diagnosed as patients; possible/ probable/ definite CCAS: 78/ 93/ 100%] and reasonable sensitivity [that is the probability that a patient is identified as a patient; possible/ probable/ definite CCAS: 95/ 82/ 46%]. Furthermore, it showed modest internal consistency using Cronbach’s alpha value (= 0.59) indicating that no test item within the scale measures the exact same domain(s) as another item. Thus, no test item is redundant. Comparing patients with pure cerebellar lesions and patients with additional extracerebellar involvement the authors found that difficulties in verbal registration and delayed verbal recall were more prominent in the latter. Therefore, poor performance in these two test items is indicative of extracerebellar involvement (“red flag”). In addition to the pass/ fail criteria which are used to screen for CCAS, a total sum score is calculated which allows for follow-up examinations in individual patients [10]. Three parallel versions B-D were developed to enable repeated assessments. In the present study preliminary German versions of the CCAS Scale are introduced, and the study protocol for their validation is presented.

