##### Study sample

For validation of version A at least 65 patients and an equal number of matched healthy controls will be recruited. About one third (≥ 25) of the patients will suffer from disorders that primarily affect the cerebellum (isolated cerebellar disease = cer-pure: 1. degenerative cerebellar disorders, e.g. spinocerebellar ataxia type 6 (SCA6); 2. focal cerebellar lesions, e.g. cerebellar stroke). The other two thirds (≥ 40 patients) will suffer from disorders with additional extracerebellar involvement (cerebellar plus disease = cer-plus: 1. degenerative cerebellar disorders, e.g. SCA1, 2 or 3; 2. focal cerebellar lesions, e.g. cerebellar stroke with additional involvement of the brain stem). Group assignment in patients with cerebellar degeneration goes by diagnosis: A genetic disease, which is known to involve extracerebellar regions, is considered a “cer-plus form”, although the clinical phenotype at the time of testing may be pure cerebellar.

An equivalent number of healthy matched participants will serve as controls. Each patient will be matched with a control participant of same sex, similar age (interval: +/− 5 years) and similar years of education (intervals: < 9 yrs., 9–10 yrs., 11–13 yrs., 14–16 yrs., > 16 yrs.). We will use the same matching criteria as in [10] except for education matching because of the different educational systems in Germany and the United States.

Parallel versions B-D will be validated in groups of 25 patients (cer-pure and cer-plus, respectively) and 25 matched healthy controls each.

Patients in this investigator-initiated, multicenter study will be recruited from the ataxia clinics at the Departments of Neurology of the University Hospitals in Aachen, Bonn, Duesseldorf, Essen, Heidelberg and Tuebingen, as well as from the MediClin Fachklinik Rhein-Ruhr in Essen, and the Departments of Neurosurgery of the University Hospital in Essen and at the Klinikum Dortmund. Essen is the coordinating site. Furthermore, we will collaborate with the “Deutsche Heredo-Ataxie Gesellschaft e.V. (DHAG)”, a patient support group, and patients will be recruited via their newsletter and webpage. Healthy controls will be recruited from patients’ families and by public bulletins.

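### The red-flag verification rests on differences between cer-pure and cer-plus patients, with no criterion to separate a memory-specific deficit from a general one

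*Protocol article*

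**What the plan says.** The Background section reports how the red flag arose in the original validation study. Patients with pure cerebellar lesions were compared with patients who had additional extracerebellar involvement, and "the authors found that difficulties in verbal registration and delayed verbal recall were more prominent in the latter". From this the article concludes that "poor performance in these two test items is indicative of extracerebellar involvement".

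The Data analysis section takes up the same idea in two consecutive sentences. The first is general: "Differences between patient groups (pure cerebellar disease vs. patients with additional extracerebellar involvement) will also be analyzed". The second states the aim: "We want to verify that difficulties in verbal registration and delayed verbal recall are indicative of extracerebellar involvement". The article gives no reference items, contrast or success criterion for this aim.

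Three features of the design bear on it:

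- **Group sizes** (Study sample): "About one third (≥ 25) of the patients will suffer from disorders that primarily affect the cerebellum", and "The other two thirds (≥ 40 patients) will suffer from disorders with additional extracerebellar involvement".
- **Group assignment** (Study sample): degenerative disease is classified by diagnosis, "although the clinical phenotype at the time of testing may be pure cerebellar".
- **Matching** (Study sample): "Each patient will be matched with a control participant of same sex, similar age". This pairs patients with controls. It does not pair cer-pure with cer-plus patients.

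Ataxia severity and disease duration are recorded. The Data analysis section uses them only as correlates of the total sum score, and single-item sub scores are among the data to be analysed.

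**The concern.** Failing any item of the scale counts towards a CCAS diagnosis. A separate red-flag label for two items adds information only if those two point to extracerebellar disease more strongly than the rest.

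A group difference on the two items answers another question, namely whether cer-plus patients score lower on them. If cer-plus patients are more impaired throughout, perhaps through longer or more severe disease, the answer is yes for every item, the memory items included. Nothing in the design removes that possibility, and no stated criterion would make the red flag fail in that case.

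At stake is how a failed memory item is read in the clinic. It could be taken as a specific pointer to extracerebellar disease when it reflects overall impairment as much as any other failed item.

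**Working it through.** The article gives no alpha, effect size or power for this comparison, so there is no figure of its own to reproduce. The group minima do add up: 25 + 40 = 65.

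**Inputs from the article.** 25 cer-pure and 40 cer-plus patients (Study sample); Cronbach's alpha of 0.59 for the original scale (Background).

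**Assumptions.** Two-sided alpha 0.05; 10 items, of which 2 are memory items; normally distributed item scores with SD 1; equal inter-item correlation r; the same deficit d in cer-plus on every item, so that memory is not special. Two values of r were used:

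- r = 0.59 / (10 − 0.59 × 9) = 0.59 / 4.69 = 0.126, from alpha = kr / (1 + (k − 1)r) with k = 10;
- r = 0.30, as a higher alternative.

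**Step 1: one memory item, by formula.** The standard error of the difference is √(1/25 + 1/40) = √0.065 = 0.255. Power is approximately Φ(d/0.255 − 1.96):

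- d = 0.3: Φ(1.18 − 1.96) = 22%
- d = 0.5: Φ(1.96 − 1.96) = 50%
- d = 0.7: Φ(2.75 − 1.96) = 78%

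**Step 2: simulation.** 10,000 runs per setting, t-tests, counting results only in the red-flag direction; the ranges cover both values of r.

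| Uniform deficit | A given memory item significant | At least one of the two | Both | Memory-minus-others contrast |
|---|---|---|---|---|
| 0.3 SD | about 21% | 35–37% | about 6% | 2–3% |
| 0.5 SD | about 49% | 69–72% | about 27% | 2–3% |
| 0.7 SD | about 77% | 92–94% | about 61% | about 2–3% |

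The nominal level in one direction is 2.5%. Group tests on the memory items pick up the general deficit, while the contrast cancels it.

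**Step 3: can the contrast detect a true memory-specific effect?** The variance of (mean of 2 items − mean of 8 items) is (1 + r)/2 + (1 + 7r)/8 − 2r = 0.625(1 − r). This gives an SD of 0.74 at r = 0.126 and 0.66 at r = 0.30. The standard errors are 0.74 × 0.255 = 0.19 and 0.66 × 0.255 = 0.17, so the 95% interval is about ±0.37 or ±0.33 SD wide. An extra memory deficit of 0.5 SD would be detected with power of about 76% and 84% respectively. The contrast is therefore usable at the planned sample size.

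**The case against.** **The text does not confine the comparison to the memory items.** This stands. The sentence on group differences is unrestricted and item sub scores are analysed. A reader might infer that only the memory items are compared, but the article does not say so. Comparing every item would make a uniform deficit easier to see, yet it would not test specificity. In 5,000 simulated runs with a uniform deficit of 0.5 SD, at least one memory item was significant while at most four of the other eight were in 34–42% of runs. With both memory items required, this happened in 10–13%. Such patterns look memory-specific when nothing is.

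**The claim is only that the items are indicative.** This stands in part. Under a general deficit, failing a memory item is still associated with cer-plus disease, so a between-group comparison does replicate the original observation. What it leaves open is whether these items deserve a label that the others do not carry.

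**The contrast may be set out in a full plan that is not shown.** That is possible, and its absence alone would be no finding. However, the article does more than leave a gap. It reports the step from a group difference to a red flag and then sets out to verify it through a comparison of the same kind.

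**The uniform deficit is hypothetical.** Correct. The article does not say that cer-plus patients are equally worse on every item, and it reports the original difference for these two items. The figures show what the stated comparison cannot exclude, not what will happen.

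**The red flag is peripheral.** It is not part of the possible/probable/definite rule, and the Perspective section names selectivity as the primary aim. This limits the weight of the point.

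**Conclusion.** The point holds in a limited form. The article sets out to verify the red flag through differences between two unmatched patient groups and states no criterion that distinguishes a memory-specific deficit from a general one.

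With the same deficit on every item, apparent confirmation on a given memory item occurs in about 21%, 49% and 77% of trials at 0.3, 0.5 and 0.7 SD. If both items must be significant, the rates are about 6%, 27% and 61%. These figures rest on the assumed alpha, item count, normality, equal correlations and uniform deficit; they change little between r = 0.126 and r = 0.30.

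A reader might go further and infer that the red flag will be confirmed whenever cer-plus patients are worse overall. The rates do not support that: at small and moderate deficits a given item misses significance in half of the trials or more. Nor would confirmation be empty, since the items would still be associated with cer-plus disease. What would remain unshown is that they mark it more than the other items do. This is a secondary analysis that should be tightened; it does not threaten the primary aim.

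**What to change.** State the red-flag analysis as a contrast between items:

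1. For each patient, standardise every item with an SD fixed in advance, for example the pooled within-group SD.
2. Take the mean of the two memory items minus the mean of the remaining items.
3. Compare this contrast between cer-pure and cer-plus patients and give a 95% confidence interval.
4. Report the group differences for all items beside it.
5. Claim a red flag specific to the memory items only if the interval excludes 0 in the expected direction. Otherwise report the association of these items with cer-plus disease as such.

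A regression of cer-plus status on memory-item failure, adjusted for the number of other failed tests, may look like an alternative, but it should not be used in its place. The count of other failures is an imprecise measure of overall impairment, so confounding remains. In simulations without any memory-specific effect (fail cut-off at −1 SD assumed), it was significant in the red-flag direction in 5–27% of runs against a nominal 2.5%.

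The cost is a few sentences and one analysis of data already collected. The downside is a stricter criterion, so the red flag will be confirmed less often.

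### The group comparison named to verify the memory red flag does not by itself show how strongly a failed item points to extracerebellar involvement in one patient

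*Protocol article*

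**What the plan says.** The Data analysis section announces the comparison: "Differences between patient groups (pure cerebellar disease vs. patients with additional extracerebellar involvement) will also be analyzed". The next sentence gives its purpose: "We want to verify that difficulties in verbal registration and delayed verbal recall are indicative of extracerebellar involvement", and labels such difficulties red flags.

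The Background takes the same step for the US data. It reports that, comparing pure cerebellar patients with those who also have extracerebellar involvement, "difficulties in verbal registration and delayed verbal recall were more prominent in the latter", and continues: "Therefore, poor performance in these two test items is indicative of extracerebellar involvement".

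The group sizes are in Study sample: "About one third (≥ 25) of the patients will suffer from disorders that primarily affect the cerebellum" and "The other two thirds (≥ 40 patients) will suffer from disorders with additional extracerebellar involvement".

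Sensitivity is defined in Data analysis as "the percentage of patients which have been correctly identified as patients", and selectivity as the corresponding percentage among controls. Both therefore concern patients against controls. Single items are examined with these measures only if the overall values fall below those of the original scale. No measure of this kind is named for cer-plus against cer-pure. On the choice of test, the section says: "Parametric or non-parametric tests will be applied depending on distribution and final sample size".

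**The concern.** A red flag is read patient by patient: this person failed the item, so extracerebellar disease is more likely. How much more likely depends on how often cer-plus patients fail relative to cer-pure patients, which is the positive likelihood ratio (LR+). A group difference shows that this ratio is probably not 1. It does not show whether it is 1.4 or 6.

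The article states both the conclusion it wants and the analysis meant to support it, and the second does not deliver the first. The German scale is intended as a bedside screen for trained healthcare personnel. If a group difference alone counts as verification, users will take the red flag as validated without knowing how much weight a failed item can bear.

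**Working it through.** The article gives no power, effect size or error rate for this comparison, so there is no figure to reproduce. The group sizes agree with the total: 25 + 40 = 65.

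**Inputs**
- From Study sample: 25 cer-pure and 40 cer-plus, the stated minima.
- Assumed, not in the article: two-sided alpha of 0.05, and all failure counts below.

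**Item scores**
- Smallest significant standardised difference: d = t(0.975; 63 df) × √(1/25 + 1/40) = 1.998 × 0.255 = 0.51.
- Under normality with equal variances, AUC = Φ(d/√2) = Φ(0.36) = 0.64.
- At the balanced cut-off, sensitivity = specificity = Φ(d/2) = Φ(0.255) = 0.60. This gives LR+ = 0.60/0.40 = 1.5.
- The Mann-Whitney threshold is nearly the same: 0.5 + 1.96 × √(66/(12 × 25 × 40)) = 0.5 + 1.96 × 0.0742 = 0.645.

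**Pass/fail items**

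LR+ = (cer-plus failing/40) ÷ (cer-pure failing/25). LR− = (cer-plus passing/40) ÷ (cer-pure passing/25). With a cer-pure and b cer-plus failures, the standard error of log LR+ is √(1/b − 1/40 + 1/a − 1/25).

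For 4/25 against 17/40: LR+ = 0.425/0.16 = 2.66. The standard error is √(1/17 − 1/40 + 1/4 − 1/25) = 0.494, which gives a 95% CI of 1.01 to 6.99. The other rows follow the same way.

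| Cer-pure failing | Cer-plus failing | Fisher p | Sensitivity | Specificity | LR+ (95% CI) | LR− |
|---|---|---|---|---|---|---|
| 15/25 | 34/40 | 0.037 | 85% | 40% | 1.4 (1.0 to 2.0) | 0.38 |
| 10/25 | 27/40 | 0.040 | 68% | 60% | 1.7 (1.0 to 2.9) | 0.54 |
| 4/25 | 17/40 | 0.032 | 43% | 84% | 2.7 (1.0 to 7.0) | 0.68 |
| 2/25 | 13/40 | 0.033 | 33% | 92% | 4.1 (1.0 to 16.5) | 0.73 |
| 1/25 | 10/40 | 0.040 | 25% | 96% | 6.3 (0.9 to 45.9) | 0.78 |

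All five tables have p between 0.03 and 0.04, yet LR+ runs from 1.4 to 6.3. The strength of evidence for a difference is about the same in each row, while the meaning of a failed item is not.

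**The case against.** The strongest objection is that the article states no rule of the kind criticised. It says that differences will be analysed and that the authors want to verify the red flag; it does not say that a significant p-value will settle the matter. With fixed item cut-offs, a comparison of failure rates rests on the same 2×2 table that yields the likelihood ratios, and the choice of summary may be fixed in a document not shown. On pass/fail data, unequal failure rates also mean that LR+ differs from 1, so the comparison does bear on the claim. All of this is correct. What remains is that the article names a conclusion about what failure indicates and only a group comparison to support it. It gives diagnostic measures with formulas for patients against controls, but none for cer-plus against cer-pure.

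A reader might infer that a significant result would leave the red flag with almost no diagnostic value. The figures do not support that. It describes only the weakest rows; the strongest point estimates show a useful rule-in sign, though an imprecise and insensitive one.

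A reader might also turn the table into predictive values. With 4/25 against 17/40, the share of cer-plus rises from 40/65 = 62% overall to 17/21 = 81% among those who fail. But 62% is a recruitment quota, so neither figure describes clinical practice. Nor should the sign be faulted for what a pass fails to exclude, since the article claims only that difficulty points towards extracerebellar involvement.

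Finally, asking only for a lower limit of LR+ above 1 would nearly repeat the p-value: 4/25 against 17/40 has p = 0.032 and a lower limit of 1.01. Only a minimum useful value adds something.

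**Conclusion.** The point holds as a mismatch between the stated conclusion and the analysis named for it. At the minimum group sizes and an assumed two-sided alpha of 0.05, a just-significant group difference is compatible with LR+ anywhere from about 1.4 to about 6, and with an AUC of about 0.64 on item scores. It therefore cannot separate a weak sign from a useful one. The failure counts are illustrations, and the AUC rests on equal-variance normality.

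The weight is moderate. Checking the red flag is not listed separately under Study aims, and the patient-against-control accuracy results do not depend on it. It is nevertheless a property that the study says it will verify, and one that users would apply to individual patients.

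**What to change.** For each of the two memory items, using the existing cut-offs, report:
- the failure rate in cer-plus patients (sensitivity) and in cer-pure patients (1 − specificity);
- LR+ and LR− with 95% confidence intervals;
- the AUC of the item score with its confidence interval.

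Before analysis, the investigators should set the minimum LR+ that they would regard as useful. The statement that the red flag is verified should rest on the size and precision of LR+ judged against that value, and not on the existence of a group difference alone.

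The change affects analysis wording only and needs no new patients, visits or data. The cost is that the intervals will be wide at these sizes, as the table shows, so the conclusion may look weaker than a p-value would.
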